### Recruitment of study population

Recruitment of patients will take place in two different settings. All eligible patients who consult a participating GP or sports physician for plantar fasciopathy will be considered for participation (prospective recruitment). On average a GP will see 8 new patients each year. It is estimated that 30 % of these patients will be willing to participate. Therefore, a total of 47 participating GP’s will be necessary to include 185 patients within two years’ time. We aim for a minimum of 50 participating GP’s or sports physicians.

All potentially eligible patients will be invited to participate in the study and will receive comprehensive information about the study. Patients that are willing to participate will fill in a reply card with their contact details and send it to the research team. The research team will then contact the interested patients and inform them further about the study and check the inclusion and exclusion criteria. If a patient is willing to participate in the study and meets all inclusion criteria and none of the exclusion criteria, he or she will sign the informed consent form and send it to the research team. The baseline questionnaire will subsequently be send to all participating patients by email. After completing the baseline questionnaire all patients will be randomized into one of the three study groups.

### Randomization procedure

After providing informed consent and baseline measurement, randomization will be performed by an independent person with the use of a computer generated randomization list using block randomization with random block sizes between 3 and 10. This sequence is kept hidden from all involved researchers. It can be expected, that patients referred by a GP and patients referred by a sports physician are different in terms of BMI and activity level. These have both been described as possible risk factors for plantar fasciopathy and therefore might influence treatment response [8]. For this reason the randomization will be stratified for type of referral (GP or sports physician). As a consequence patients from both populations will be equally distributed across the three treatment arms.

### Interventions

Patients (*n* = 47) randomized to the usual care group will receive an information booklet with general information on plantar fasciopathy. This information booklet will contain information on the use of pain medication and possible stretching and strength exercises (plantar specific stretching identical to the protocol used by DiGiovanni et al. [25] and unilateral heel raises adapted from exercises as described by Rathleff et al. [26]) that are considered to be helpful for all patients with plantar fasciopathy. The patients in this group will not be referred to a podiatrist. They will receive usual care as provided by their GP or sports physician.

Patients randomized to the custom made insole group (*n* = 69) and the placebo insole group (*n* = 69) will a be referred to a podiatrist. All patients that are referred to a podiatrist will additionally receive the information booklet identical to the usual care group as described above. The first appointment with the podiatrist will take place as soon as possible after randomization (preferably within 1 week). All patients referred to a podiatrist will receive a standardized intake with identical procedures. These procedures have been discussed and agreed upon with the participating podiatrists in a consensus meeting. If a podiatrist could not attend they were given elaborate explanation and the opportunity to give input during a telephone conference.

The standardized intake at the podiatrist will consist of an examination of the posture of the foot using the standardized Foot Posture Index [27], the Hubscher test [28], the navicular drop test [29] and the range of motion in the tarsometarsal joint and the first metatarsophalangeal joint (MTP-I) as measured with a goniometer. The podiatrists will report for each patient, whether they agree with the indication for orthotic insoles as established by the GP or sports physician. A 3D imprint of the feet of all patients visiting a podiatrist will be made. All these examinations will take place during the first appointment, which will take approximately 50 min. During this first appointment the podiatrist is blinded for the outcome of the randomization. The podiatrist will be informed about the allocated treatment, after the first appointment.

All patients referred to a podiatrist will have a second appointment within 2 weeks after the intake, of approximately 10 min to pick up their insole. Patients randomized to the custom made insole group will receive a custom made insole. Patients randomized to the placebo insole group will receive a placebo insole (Fig. 2), that has been custom designed for their foot (based on a 3D imprint of their foot) without providing therapeutic effect, but still have the visual effect of a podiatric insole. See Fig. 3 for the standardized production procedure of the placebo insole. All placebo insoles will be produced by the same podiatrist according to this protocol after receiving the 3D imprint from the different podiatrists. The placebo insoles will then be sent back to the different podiatrists to give to the patients. The custom made insole will always be patient tailored, but will be produced according to usual podiatric care by the different podiatrists. A third checkup appointment will be offered to the patients in the placebo insole group and the custom made insole group after 12 weeks as part of the usual podiatric care. Podiatrists with a practice near participating GP’s and sports physicians were approached to participate in the study. For every participating GP or sports physician a nearby podiatrist was found. In total 49 podiatrists have agreed to participate in this study.

**Fig. 2 Fig2:**
[figure not shown]
The placebo insole

**Fig. 3 Fig3:**
[figure not shown]
The procedure for producing the placebo insole

### The use of co-intervention

In the 6 months of follow-up the GP’s and sports physicians will provide their usual treatment to the patients. They are discouraged from referring patients in the usual care group to the podiatrist during follow-up. Patients who receive co-interventions, will not count as a failure in the analysis. The podiatrists will be allowed to give advice on shoes and exercises as part of the podiatric intervention. Patients will report co-interventions in the questionnaires.

### Study outcomes

The primary outcome will be the change from baseline to 12 weeks follow-up in pain severity at rest and during activity on a 0–10 numerical rating scale (NRS). Secondary outcome measures include foot function as measured by the Foot Function Index at 6, 12 and 26 weeks follow-up, perceived recovery measured on a 7-point Likert scale (ranging from “worse than ever” to “completely recovered”, those who rate themselves as “slightly recovered” to “worse than ever” will be deemed not recovered) at 6, 12 and 26 weeks follow-up, pain at rest and during activity at 6 and 26 weeks follow-up and cost-effectiveness of the intervention at 26-weeks follow-up.

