### Sample size

Based on the RCT of Landorf et al. (2006) [18] –pain score 63.4 (SD 21.5), with a difference in pain score of 10.5 (on a scale of 0–100) – it is estimated that with a power of 80 % and an alpha of 0.05 (two-sided), it is possible to detect an effect size of 0.5 with 10.5 points difference on the pain score between patients with a placebo insole and custom made insole with 63 patients in each study group. In addition, a larger difference is expected between the custom made insole group and the usual care group. With a 12-point difference and identical means and SDs, a total of 44 patients are needed per group. A Bonferroni correction will be performed for the secondary comparisons to the usual care group. Taking a loss to follow-up of 10 % into account, a total of 185 patients with plantar fasciopathy (69 in custom made group, 69 in placebo group and 47 in usual care group) will be included in the trial.

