### Baseline measurement

The baseline questionnaire will include questions on demographics (age, gender, BMI, education level, work and comorbidities), duration of pain, work activity (type, magnitude and load), sports activities (including the validated questionnaires SQUASH and Tegner) [30, 31], general health (SF12) [32], quality of life (EuroQol 5 dimensions) [33], neuropathic pain (DN4) [34], function (Foot Function Index (FFI)) [35], disability (Manchester-Foot Pain and Disability Index questionnaire (MPDI) [36], pain at rest and during activity (11-point NRS-scale) [37], incidence of falling, type of shoes and previously received medical care.

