### Data analysis

Differences between the intervention groups will be analyzed following the intention-to-treat principle. Linear regression techniques for repeated measurements will be used to compare pain severity between the intervention group and control groups, which take the correlation of multiple measurements within one patient into account. A Bonferroni correction will be performed for the secondary comparisons to the usual care group. The analysis will be adjusted for potential confounders (at least including age, gender, BMI and activity level).

Recovery, pain scores and function will be analyzed using regression techniques for repeated measures using generalized mixed models.

Mean direct, indirect and total costs will be estimated and compared between the three study groups. Because costs will not be normally distributed, 95 % confidence intervals for the differences in mean costs will be obtained by bias corrected and accelerated bootstrapping (2000 replications). Differences in costs and differences in recovery will be included in a cost-effectiveness ratio, which estimates the additional costs to completely recover one patient.

Confidence intervals for the cost-effectiveness ratio will be calculated with bootstrapping, using the bias-corrected percentile method with 5000 replications. An incremental cost-effectiveness ratio will be estimated of the incremental costs to recover one patient. Uncertainty of this ratio will be evaluated by presenting a cost-effectiveness plane and sensitivity analyses will be performed to check the robustness of the results. An acceptability curve will also be presented.

Pre-defined subgroup analysis will be performed in patients with a long (>12 months) and short (<12 months) duration of the complaints at baseline, in patients with a low, moderate or high total activity score derived from the SQUASH questionnaire (in tertiles), in patients recruited in general practice and by sports physicians and in patients where the podiatrist agrees with the indication for orthotic insoles and in patients where the podiatrist does not.

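### The primary outcome is change from baseline, but baseline pain is not named as an adjustment variable; unless it enters the model, precision is lost, and power is below 80% if the baseline to 12-week correlation is under about 0.5

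*Protocol article*

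**What the plan says.** Under Study outcomes, the article defines the endpoint: "The primary outcome will be the change from baseline to 12 weeks follow-up in pain severity", scored on a 0–10 numerical rating scale.

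Under Data analysis, pain severity is to be compared between groups by linear regression for repeated measurements, allowing for within-patient correlation. On covariates it says: "The analysis will be adjusted for potential confounders (at least including age, gender, BMI and activity level". Baseline pain is not among the four named variables, but the list is a stated minimum. Nothing says whether baseline pain is a covariate, one of the repeated outcomes, or present only through the change score.

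Baseline pain is available. Under Baseline measurement the questionnaire includes "pain at rest and during activity (11-point NRS-scale", and Recruitment of study population places randomization after that questionnaire.

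The Sample size section takes its inputs from an earlier trial: "pain score 63.4 (SD 21.5), with a difference in pain score of 10.5". It concludes that "it is possible to detect an effect size of 0.5 with 10.5 points difference on the pain score", this being the contrast "between patients with a placebo insole and custom made insole with 63 patients in each study group". The SD is attached to a pain score. No SD of change and no correlation between baseline and follow-up is given. The Discussion adds only that the figures were rescaled to the 0–10 scale.

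**The concern.** Baseline pain is usually a strong predictor of later pain. A change score subtracts it with a fixed coefficient of 1. With equal SDs at the two times, the best linear coefficient is r, which is below 1. An unadjusted change score therefore over-corrects for baseline and carries avoidable noise. Conditioning on baseline removes that noise and uses only data the trial already collects.

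The sample size adds a second question. If 21.5 is the spread of a single score and the endpoint is a change, the two have different SDs unless r = 0.5. With r below 0.5 the change is the more variable quantity, and 63 per group no longer gives the stated power. At stake are the precision and power of the custom-made versus placebo comparison.

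**Working it through.** **Inputs from the article.** Sample size section: two-sided alpha 0.05, power 80%, difference 10.5, SD 21.5 (0–100 scale), effect size 0.5, 63 per group.

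**Assumptions.** r is not given, so a range is shown. SDs at baseline and 12 weeks are taken as equal. The 63 per group is treated as the number analysed. The four named covariates are ignored. A normal approximation is used.

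**Step 1: reproduce the stated figure.**
n = 2 × (1.96 + 0.8416)² / 0.5² = 62.8, so 63 per group. Power at 63 is Φ(0.5 × √(63/2) − 1.96) = Φ(2.806 − 1.96) = 80.1%. The article's figure reproduces from the rounded effect size 0.5.

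**Step 2: SD under each analysis, if 21.5 is the SD of one score.**
- Unadjusted change: SD × √(2(1 − r))
- Baseline-adjusted: SD × √(1 − r²)
- Variance ratio, change to adjusted: 2(1 − r)/(1 − r²) = 2/(1 + r), which is 1.54 at r = 0.3, 1.33 at 0.5 and 1.18 at 0.7

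The change SD equals the score SD when 2(1 − r) = 1, that is, at r = 0.5.

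**Step 3: power at 63 per group, effect size 0.5.** Power = Φ(2.806/k − 1.96), where k is the SD multiplier from Step 2. At r = 0.3, for example, k = √1.4 = 1.183 for change gives Φ(0.412) = 66.0%, and k = √0.91 = 0.954 for adjusted gives Φ(0.982) = 83.7%.

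| r | Power, change | Power, adjusted | n per group for 80%, change | n per group for 80%, adjusted |
|---|---|---|---|---|
| 0.2 | 60.2% | 81.7% | 101 | 61 |
| 0.3 | 66.0% | 83.7% | 88 | 58 |
| 0.4 | 72.6% | 86.5% | 76 | 53 |
| 0.5 | 80.1% | 90.0% | 63 | 48 |
| 0.6 | 88.1% | 93.9% | 51 | 41 |
| 0.7 | 95.2% | 97.6% | 38 | 33 |

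**Step 4: the repeated-measures model.** For a model of baseline and 12 weeks with baseline pain as one of the outcomes, the result depends on how the baseline means are treated. With 63 per group and the unrounded 10.5/21.5 = 0.488:
- common baseline mean: 82% power at r = 0.3 and 89% at r = 0.5, the same as baseline adjustment
- separate baseline means, testing change: 64% and 78%, the same as the change score

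**Step 5: if 21.5 is already the SD of a change.** Change-score power is then the planned 80.1% (effect size 0.5), and adjustment multiplies the SD by √((1 + r)/2). At r = 0.3 this gives Φ(2.806/0.806 − 1.96) = 94%, and at r = 0.7 Φ(2.806/0.922 − 1.96) = 86%. Planned power stands, and adjustment adds to it.

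**The case against.** The strongest reply is that the article does not commit to an inefficient analysis. Study outcomes defines an endpoint, whereas Data analysis describes a repeated-measures regression of pain severity with an open covariate list. Baseline pain may be added under that wording, and a model with a common baseline mean would be as efficient as baseline adjustment. An article may also leave such detail to a fuller plan. This stands to the extent that a reader may not infer that a raw change-score comparison is planned or that baseline pain is excluded. It does not remove the point. The article does fix the outcome as a change and does choose a minimum covariate set, and that set omits a variable likely to be highly prognostic. Step 4 shows that both the efficient and the inefficient model fit the present wording.

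A reader might also infer that the result would be biased. It would not: under randomization the change-score contrast is unbiased, and chance imbalance in baseline pain affects the precision of the realised estimate, not validity.

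Nor do the documents show that the trial is underpowered. That needs r below about 0.5 and 21.5 to be the SD of a single score. The article settles neither, and at r = 0.6 or above the unadjusted change score exceeds 80%.

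Finally, power computed from 10.5/21.5 = 0.488 is a little lower throughout (78.3% at r = 0.5 with 63 per group). That gap comes from rounding the effect size to 0.5, not from the change score, so the table uses the article's own 0.5.

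**Conclusion.** The concern holds as one of precision and specification. As written, the plan permits an analysis of change that does not condition on baseline pain. Its variance would be 2/(1 + r) times that of the adjusted analysis, a loss at every r below 1 when the SDs are equal.

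The effect on power is conditional. On the article's effect size and 63 per group, with 21.5 read as a single-score SD, unadjusted power is about 66% at r = 0.3, 80% at r = 0.5 and 95% at r = 0.7. The adjusted figures are about 84%, 90% and 98%. The adjusted analysis keeps at least the stated 80% throughout the range shown. The unadjusted one keeps it only from about r = 0.5 upward.

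**What to change.** In Data analysis, name baseline pain as a covariate in the primary model, or specify a longitudinal model in which the groups share a common baseline mean. State that the treatment contrast at week 12 is the primary estimate. The endpoint can still be reported as change: once baseline pain is a linear covariate, modelling the change or the 12-week score gives the same treatment estimate.

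In Sample size, state whether 21.5 is the SD of a score or of a change, and which baseline to 12-week correlation is assumed.

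The cost is a few sentences, fixed before unblinded data are seen. No new measurements and no additional patients are needed.

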### Measurements

During a 6 month follow-up the participating patients will be asked to complete a total of six questionnaires. At baseline, at 2 weeks, at 4 weeks, at 6 weeks, at 12 weeks and at 26 weeks of follow-up. The participants will receive an e-mail that contains a secured hyperlink to the questionnaire, using the survey application Lime Survey. Phone calls and reminder emails will be used to minimize loss to follow-up and missing data.

### Baseline measurement

The baseline questionnaire will include questions on demographics (age, gender, BMI, education level, work and comorbidities), duration of pain, work activity (type, magnitude and load), sports activities (including the validated questionnaires SQUASH and Tegner) [30, 31], general health (SF12) [32], quality of life (EuroQol 5 dimensions) [33], neuropathic pain (DN4) [34], function (Foot Function Index (FFI)) [35], disability (Manchester-Foot Pain and Disability Index questionnaire (MPDI) [36], pain at rest and during activity (11-point NRS-scale) [37], incidence of falling, type of shoes and previously received medical care.

### Follow-up measurements

The 2, 4 and 6 week questionnaires will include questions on recovery on a 7-point Likert scale [38], pain at rest and during activity (NRS) and foot function (FFI). The questionnaires at 12 and 26 weeks will include these questions as well and will additionally include questions on general health (SF12), quality of life (EuroQol), direct cost (medical costs: health care visits, medication, medical devices), indirect cost (absence from work, inability to work) and current activity level. The patients randomized to the two podiatrist groups will also complete questions on patient satisfaction and compliance to treatment in the questionnaires at 12 and 26 weeks. In the 26 week questionnaire we will additionally ask all patients allocated to podiatric treatment to report their expectation regarding the type of insole they received, in order to assess the successfulness of blinding.

### Data analysis

Differences between the intervention groups will be analyzed following the intention-to-treat principle. Linear regression techniques for repeated measurements will be used to compare pain severity between the intervention group and control groups, which take the correlation of multiple measurements within one patient into account. A Bonferroni correction will be performed for the secondary comparisons to the usual care group. The analysis will be adjusted for potential confounders (at least including age, gender, BMI and activity level).

Recovery, pain scores and function will be analyzed using regression techniques for repeated measures using generalized mixed models.

Mean direct, indirect and total costs will be estimated and compared between the three study groups. Because costs will not be normally distributed, 95 % confidence intervals for the differences in mean costs will be obtained by bias corrected and accelerated bootstrapping (2000 replications). Differences in costs and differences in recovery will be included in a cost-effectiveness ratio, which estimates the additional costs to completely recover one patient.

Confidence intervals for the cost-effectiveness ratio will be calculated with bootstrapping, using the bias-corrected percentile method with 5000 replications. An incremental cost-effectiveness ratio will be estimated of the incremental costs to recover one patient. Uncertainty of this ratio will be evaluated by presenting a cost-effectiveness plane and sensitivity analyses will be performed to check the robustness of the results. An acceptability curve will also be presented.

Pre-defined subgroup analysis will be performed in patients with a long (>12 months) and short (<12 months) duration of the complaints at baseline, in patients with a low, moderate or high total activity score derived from the SQUASH questionnaire (in tertiles), in patients recruited in general practice and by sports physicians and in patients where the podiatrist agrees with the indication for orthotic insoles and in patients where the podiatrist does not.

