### Objectives

The primary objective of our study is to examine the effectiveness of custom made insoles by a podiatrist, compared to placebo insoles and compared to usual care in general practice and sports medicine alone in patients with plantar fasciopathy in terms of pain.

The secondary objective of our study is to examine the cost-effectiveness of custom made insoles by a podiatrist, compared to usual care in patients with plantar fasciopathy.

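### Bonferroni for the usual-care comparisons is valid, but Holm gives the same error control and is never less powerful; the gain is 0 to about 5 points per test, depending on a family the article does not state

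*Protocol article*

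**What the plan says.** The protocol article gives the multiplicity rule twice in the same words, under Sample size and under Data analysis: "A Bonferroni correction will be performed for the secondary comparisons to the usual care group". It uses the plural and does not count or list the comparisons.

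The primary objective concerns custom made insoles "compared to placebo insoles and compared to usual care in general practice and sports medicine alone". Placebo v usual care is not named there. The primary outcome under Study outcomes covers two pain ratings, at rest and during activity.

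For the sample size, the article takes "pain score 63.4 (SD 21.5), with a difference in pain score of 10.5" from the earlier trial, at 80 % power and two-sided alpha 0.05. For usual care it says: "With a 12-point difference and identical means and SDs, a total of 44 patients are needed per group". After 10 % loss is allowed for, the arms are 69 custom, 69 placebo and 47 usual care.

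**The concern.** Single-step Bonferroni compares every p-value in the family with alpha/k. Holm does so only for the smallest p-value. Once that is rejected, the next is compared with alpha/(k-1), and so on. Both hold the familywise error at alpha under any dependence between the tests, and Holm rejects everything that Bonferroni rejects. For p-values, then, Bonferroni can only lose.

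Usual care is the smallest arm, and custom v usual care is one of the two comparisons in the primary objective. A real difference on this comparison should not be missed through the choice of correction if an equally strict procedure costs one sentence.

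**Working it through.** **Inputs.** Difference 12 points for custom v usual care, difference 10.5 for custom v placebo and SD 21.5 come from Sample size. Evaluable patients after 10 % loss: 69 x 0.9 = 62 and 47 x 0.9 = 42. Familywise alpha is 0.05, two-sided. Placebo v usual care is not given; 12 - 10.5 = 1.5 points is implied. The size of the family, the effect on each pain rating and the correlation between ratings are not in the article, so they are varied as assumptions.

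**The plan's own figures** (normal approximation).
- Custom v placebo with effect size 0.5: n = 2 x (1.960 + 0.842)^2 / 0.5^2 = 62.8, so 63 per group, as stated.
- Custom v usual care, stated as 44: 42 usual-care patients are needed against 63 custom at alpha 0.05, and 44 v 63 has 81.1 % power. Equal groups with the effect rounded to 0.6 give 2 x 7.849 / 0.36 = 43.6, so 44. Literal 12/21.5 with equal groups gives 51. At alpha 0.025 the need would be 59 (against 63) or 62 (equal groups).
- The 44 therefore fits an uncorrected alpha of 0.05.

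**Power for custom v usual care at 62 v 42.** The expected test statistic is 12 / (21.5 x sqrt(1/62 + 1/42)) = 2.793.
- At 0.05: Phi(2.793 - 1.960) = 79.8 %.
- At 0.025 (Bonferroni, k = 2): Phi(2.793 - 2.241) = 70.9 %.
- At 0.0125 (Bonferroni, k = 4): Phi(2.793 - 2.498) = 61.6 %.

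**What Holm adds.** For k = 2, Holm rejects test *i* if p_i < 0.025, or if p_i < 0.05 and p_j < 0.025. The gain for test *i* is the probability that p_i lies between 0.025 and 0.05 while p_j < 0.025. For custom v usual care it cannot exceed 79.8 - 70.9 = 8.9 points, and it cannot exceed the probability that the other test is rejected at 0.025.

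**Results by family** (simulated correlated normal test statistics). The correlation between the two contrasts, which share the usual-care arm, is (1/42) / (1/62 + 1/42) = 0.60.

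| Family | Test | Bonferroni | Holm | Gain (points) |
|---|---|---|---|---|
| Custom v usual care, one test | that test | 79.8 % | 79.8 % | 0 |
| Rest and activity pain, custom v usual care, 12 points on both, correlation 0.3 to 0.7 | each rating | 71 % | 76-77 % | about 5 |
| Custom and placebo v usual care, 12 and 1.5 points | custom v usual care | 71 % | 71 % | under 0.1 |
| same | placebo v usual care | 3.4 % | 5.9 % | about 2.5 |
| Two contrasts by two ratings, 12 and 1.5 points, correlation 0.5 between ratings | custom v usual care, each rating | 62 % | 64 % | about 2 |

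The third row is small for a plain reason. With a 1.5-point effect, placebo v usual care is rejected at 0.025 only 3.4 % of the time, and in almost all of those cases custom v usual care is already significant at 0.025.

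**Sensitivity.**
- Two contrasts (63/63/44 patients): the gain for custom v usual care is 0.5 points if placebo beats usual care by 6 points, 3.5 if by 10.5 and 5.0 if by 12.
- Two ratings with unequal effects of 12 and 8 points (assumed): the weaker rating gains 8 to 9 points and the stronger 1 to 3.

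**The case against.** The strongest reply is that nothing here is wrong. Bonferroni is prespecified, stated consistently in both sections and valid under any dependence. It also yields simple simultaneous confidence intervals that always agree with its tests, which Holm does not. All of that stands, so the point is one of efficiency and not of error control. A reader might infer that the power is given up for nothing; the matching intervals are a real return.

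The second reply concerns size. A reader might infer a general loss of 5 to 10 points. The plan's own figures do not support that. A gain of 5 points for custom v usual care within the two-contrast family needs placebo to beat usual care by about 12 points, which would make custom and placebo equal and contradict the 10.5 points on which the trial is sized. Larger figures need 12 points on all four tests, which conflicts in the same way, or success defined as every test significant, a criterion the plan does not set. The 5-point figure is consistent with the plan only if the family is the two pain ratings with 12 points on each. The correction is worded by comparison group and not by rating, so that reading is possible but not stated.

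Neither reply changes the fact that, for the tests themselves, Holm is never worse.

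**Conclusion.** The point holds as a cheap improvement. Holm gives the same familywise error control as the planned Bonferroni rule with no extra assumption and at least as much power. At 62 v 42 patients, SD 21.5 and two-sided familywise alpha 0.05, the gain is zero for one comparison and about 5 points per test for two ratings at 12 points each. For two contrasts at 12 and 1.5 points it is under 0.1 point (custom) and about 2.5 points (placebo), and for two contrasts by two ratings it is about 2 points per custom v usual care rating. The family may be defined in an analysis plan that is not shown, so its absence from the article is not itself a criticism.

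Two further inferences should be resisted. Holm does not restore 80 % power for custom v usual care. The 44 fits an uncorrected 0.05, and if two contrasts are corrected, power stays near 71 % under either procedure. Nor does the change touch the cost-effectiveness analysis, which rests on bootstrap intervals, a cost-effectiveness plane and an acceptability curve, with no stated Bonferroni correction.

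**What to change.** Under both Sample size and Data analysis, replace the Bonferroni correction for the usual-care comparisons with: *the Holm procedure (two-sided familywise alpha 0.05)*. Report Bonferroni simultaneous intervals beside the Holm p-values.

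Keep custom v placebo outside this family, as the plan now does. Putting it in a Holm family with custom v usual care (63/63/44 patients) would raise the latter from 72.6 % to 77.5 %, but would lower the primary contrast from 78.3 % to 75.0 %.

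The cost is one sentence in each place and no patients. The downside is that a Holm-significant comparison may carry a Bonferroni interval that includes zero; the plan should say in advance that the Holm p-value decides the test.
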